## Abstract

**Background:**

Despite success in HIV treatment, diagnosis and management of hypertension (HTN) and cardiovascular disease (CVD) remains suboptimal among people living with HIV (PLWH) in Botswana, with an overall HTN control of only 19% compared to 98% HIV viral suppressed. These gaps persist despite CVD primary care national guidelines and availability of free healthcare including antihypertensive medications. Our study aims to develop and test strategies to close the HTN care gap in PLWH, through integration into HIV care, leveraging the successful national HIV care and treatment program and strategies.

**Methods:**

The InterCARE trial is a cluster randomized controlled hybrid type 2 effectiveness-implementation trial at 14 sites designed to enroll 4652 adults living with HIV and HTN plus up to 2326 treatment partners. Primary outcomes included effectiveness (HTN control) and implementation outcomes using the Reach Effectiveness Adoption Implementation and Maintenance framework, with explanatory mixed methods used to understand variability in outcomes.

InterCARE trial’s main strategies include healthcare worker HTN and CVD care training plus long-term practice facilitation, electronic health record (EHR) documentation of key indicators and use of reminders, and use of treatment partners to provide social support to people living with HIV and HTN. InterCARE started with formative research to identify contextual factors influencing care gaps using the Consolidated Framework for Implementation Research. Results were used to adapt initial and develop additional implementation strategies to address barriers and leverage facilitators. The package was pilot tested in two clinics, with findings used to further adapt or add strategies for the clinical trial.

**Discussion:**

If successful, the InterCARE model can be scaled up to HIV clinics nationwide to improve diagnosis, management, and support in Botswana. The trial will provide insights for scale-up of HTN integration into HIV care in the region.

**Trial registration:**

ClinicalTrials.gov reference NCT05414526. Registered 18 May 2022, https://clinicaltrials.gov/study/NCT05414526?term=NCT05414526.&rank=1.

## World Health Organization Trial Registration Data Set {2b}

**Table Tabb:** 

Data category	Information
Primary registry and trial identifying number	ClinicalTrials.gov NCT05414526
Date of registration in primary registry	18 May 2022
Secondary identifying numbers	InterCARE project
Source(s) of monetary or material support	United States of America National Institute of Health (NIH) via the National Heart, Lung and Blood Institute (NHLBI):
Primary sponsor	United States of America National Institute of Health (NIH) via the National Heart, Lung and Blood Institute (NHLBI):
Secondary sponsor(s)	N/A
Contact for public queries	[name]. [contact]
Contact for scientific queries	[name]. [contact]
Public title	Integrating Hypertension and Cardiovascular Diseases Care Into Existing HIV Services Package in Botswana (InterCARE)
Scientific title	Designing an implementation science clinical trial to Integrate hypertension and cardiovascular diseases care into existing HIV services package in Botswana (InterCARE)
Countries of recruitment	Botswana
Health condition(s) or problem(s) studied	Hypertension, Cardiovascular disease, HIV
ntervention(s)	Active Comparator: Integrating hypertension and cardiovascular diseases care (InterCARE). Placebo comparator: standard of care/routine care
Key inclusion and exclusion criteria	Inclusion 1) aged between 20 and 75 years old 2) have documented HIV infection and on ART 3) confirmed diagnosis of HTN or elevated systolic blood pressure or diastolic blood pression 4) registered client at the selected clinics All sexes eligible, doesn’t’ accept healthy volunteers Exclusion Documented as having a diagnosis of dementia in clinic records, or unable or unwilling to provide informed consent.
Study type	Mixed-methods, cluster randomized control type II hybrid effectiveness-implementation trial
Date of first enrolment	January 2023
Target sample size	4,652 PLWH with HTN across the intervention and control sites. Up to 2,326 treatments partners
Recruitment status	Follow up
Primary outcome(s)	Effectiveness (proportion of PLHIV with diagnosed hypertension receiving anti-hypertensive medication with controlled blood pressure) Implementation (Proportion of clinic encounters in EHR where anti-hypertensive medications are prescribed if indicated)
Key secondary outcomes	Reach (proportion of PLWHIV with hypertension who are aware of their hypertensive status) Adoption (proportion of PLWHIV with HTN prescribed anti-hypertensive medications in the EHR) Implementation fidelity (audit of intervention implementation as designed) Implementation feasibility (ability to implement integrated HIV/HTN care, HIV/HTN/CVD care etc.) Implementation acceptability (patient and provider survey and interviews) of the implementation strategy. Maintenance (provider and patient perceptions of ability to maintain plus change in blood pressure control from 12-24 months of the trial).

## Introduction

### Background and rationale {6a}

Globally, people living with HIV (PLWH) have longer life expectancy due to improvement in access to HIV care, including antiretroviral therapies (ART). As lifespan has increase, this population is aging, with growing rates of cardiovascular diseases (CVDs) and other age-related morbidities. An estimated 24% of PLWH have hypertension (HTN), making it one of the most prevalent modifiable risk factors for CVD in this population [1]. HTN occurs among younger individuals compared to the general population, with a median age of about 38 years in most cohorts of PLWH in Sub-Saharan Africa [2]. Gaps in diagnosis and treatment exist, with rates of treatment and control are well below 50% among PLWH with HTN in Botswana [3]. This gap in HTN care extends to other countries such as Uganda, where 88% of PLWH and HTN were initiated on blood pressure treatment, but only 24.3% achieved blood pressure control [4]. These lower rates of HTN treatment and control are in contrast to the success of Botswana in surpassing the 2022 Joint United Nations Program on HIV/AIDS (UNAIDS) targets of 95% diagnosis, treatment, and viral suppression [3]. Therefore, innovative strategies are required to leverage the successes of the HIV program to address NCD challenges such as hypertension among PLWH and HTN.

One in 4 adult PLWH in Botswana have HTN, making it one of the leading CVD risk factors in this population [5, 6]. Botswana recognized the increased burden of non-communicable diseases (NCDs), reflected in the national Multisectoral Strategy for the Prevention and Control of NCDs published by the Ministry of Health (MOH) [7]. The strategy included national guidelines for HTN diagnosis and treatment and free universal healthcare including HTN medications. The strategy also included recommendations for integrating HTN into HIV care, leveraging the existing HIV care program plus electronic documentation of HTN-related national indicators. However, little is known about the specific strategies required to achieve this goal in Botswana.

### Objectives {7}

The hypotheses of this study are as follows:Integrating hypertension care within an existing HIV care platform is feasible, acceptable, and associated with early improvement in the hypertension cascade of care but will require substantial change in patient and provider attitudes, knowledge, and clinic operations.The study’s proposed multi-component intervention will largely be successful, as measured by the Reach, Effectiveness, Adoption- Implementation, Maintenance (RE-AIM) framework.

### Trial design {8}

The INTEgrating hypeRtension and cardiovascular diseases CARE into existing HIV services package in Botswana** (**InterCARE) trial is a mixed-methods, cluster randomized control type II hybrid effectiveness-implementation trial in fourteen HIV clinics in Botswana.

## Methods: participants, interventions, and outcomes

### Study setting {9}

This study will be conducted within the ~ 497 Botswana national HIV clinic/health post system. The nationwide HIV clinics serves > 320,000 PLWH and utilizes both paper-based and electronic health records. At each HIV clinic, staffing typically includes 0–2 medical officers [sometimes resident and other times on rotation or available telephonically from other health facilities], 1–4 nurses, pharmacy technician (sometimes), variable number of nursing assistants, phlebotomist, and a part-time social worker/health welfare educator. We will choose 7 pairs of clinics from 30 communities which participated in the Botswana Combination Prevention Project (BCPP) [8]. We will obtain updated data on all 30 BCPP communities and match HIV clinics on number and type of staffing and number of patients total by using the technique of calculating Euclidean distances between all possible pairs to determine the best (closest) two matches. We may also use other factors for matching, such as extent of existing pharmacy, laboratory, and rural/urban location, if we find that factors related to blood pressure control may vary across clinics.

### Eligibility criteria {10}

Patients are eligible if they (1) are aged between 20 and 75 years old, (2) have documented HIV infection and are on ART, (3) have a confirmed diagnosis of HTN or elevated systolic blood pressure (SBP) ≥ 140 or diastolic blood pression (DBP) ≥ 90 mmHg (or SBP ≥ 130 or DBP 80 mmHg if they have diabetes mellitus or chronic kidney disease), and (4) are a registered client at the selected clinics. PLWH are not eligible if they are documented as having a diagnosis of dementia in clinic records or if they are unable or unwilling to provide informed consent. PLWH and HTN will be selected for enrolment using a purposive random sampling method by trained research assistants at each site.

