### Intervention description {11a}

The InterCARE package consists of three strategies adapted from the successful Botswana HIV program: provider training, use of an EHR, and treatment partners.*Electronic health records (EHR)*: at the beginning of the national ART program, Botswana developed a local EHR, patient information management system (PIMS) that has been used to document outcomes of the national ART program [9], and optimized for an HIV prevention trial [3]. However, this EHR system has not been used for other chronic diseases in Botswana. The use of clinical decision support in EHR is generally associated with improvement in quality of care [10], but data are mixed for CVD risk factors monitoring. This strategy can address barriers in knowledge and adoption of CVD risk assessment and HTN management and monitoring of national strategy key NCD care indicators.*Treatment partners*: many national HIV programs including in Botswana have utilized community members as treatment partners for PLWH [11–15]. In Botswana, the use of treatment partners has been associated with improved HIV medication adherence and viral suppression [11]. As with other chronic lifestyle-related medical conditions, family or presence of close other persons is recommended as part of an evidence-based strategy to assist those with hypertension to care for themselves, provide social support, promote adherence to lifestyle changes/medications, etc. [11]. This American Heart Association (AHA) evidence-based strategy for social support has not been adapted for PLWH with HTN in Botswana [16]. InterCARE participants will be given guidance on how to choose an appropriate treatment partner for their HTN support. Treatment partners will attend training along with the participant on how to provide social, emotional, and adherence support.*HTN/CVD training*: the highly successful KITSO training program (healthcare curriculum for HIV care in Botswana) is in use at more than 400 peri-urban and rural HIV clinics in Botswana but has never been leveraged to enhance NCD care for PLWH in Botswana. Building on the model, a dedicated healthcare provider curriculum and certification on hypertension control and CVD care among PLWH was developed for use in InterCARE, reflecting national and international guidelines for HTN management. The training will be provided at the start of InterCARE and again annually. Application and ongoing learning will be supported through practice facilitation by research nurses during regularly scheduled visits and monthly data audit and feedback.

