### Recruitment {15}

Strategies for achieving adequate participant enrolment to reach target sample size is to enroll sites in pairs, i.e., one controlled site will be enrolled with one intervention site simultaneously. Before enrolment, community/stakeholder engagement followed by pre-implementation surveys will be done for each site. Training of providers on protocol and EHR changes as well as hypertension management will be done at intervention sites. Participants will be mainly enrolled during their IDCC visit (HIV-related clinic visit). To scale up enrolment, participants will also be enrolled when they came for other HIV-related services at other departments such as laboratory and pharmacy.

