## Assignment of interventions: allocation

### Sequence generation {16a}

Using the coin flip randomization method, 14 clinics will be randomized to a trial arm (*n* = 7 intervention, *n* = 7 control). Since patients are registered at one clinic only (and do not tend to visit more than one clinic), participants cross-over between intervention and control clinics is unlikely; hence, we do not expect contamination to become an issue.

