### Concealment mechanism {16b}

IRB approval was first granted centrally for all potentially eligible sites. Then, facility assessment readiness and willingness to participate were done. Once a rolling list of 14 sites had been reached, a study launch site was done systematically as pairs (control and associated intervention sites). Ultimately, our approach allowed for allocation concealment until randomization and study activation team was ready to activate the site.

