### Implementation {16c}

Our research assistants will enroll participants who will then be exposed to the implementation strategies by healthcare providers at their HIV clinic.

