## Assignment of interventions: blinding

### Who will be blinded {17a}

There was no blinding, as this is not feasible because our trial is focused on strategies to improve HTN/CVD care in the intervention sites; thus, both providers and participants ought to be aware. It was also difficult to blind our analysts as our biostatisticians work closely with the clinical operations team to track and document variability across sites, and recommend continuous adaptations, and gain understanding of why interim site data is changing.

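### Participants are selected after clinic allocation, in an unblinded trial and by an unclear sampling rule, and no planned analysis addresses differences in hypertension status at entry

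*Protocol article*

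**What the plan says.** The unit of randomisation is the clinic: "14 clinics will be randomized to a trial arm" (Sequence generation {16a}). Concealment is described at clinic level only: "our approach allowed for allocation concealment until randomization and study activation team was ready to activate the site" (Concealment mechanism {16b}). Sites start as labelled pairs: "one controlled site will be enrolled with one intervention site simultaneously" (Recruitment {15}). The same section lists the preparation of intervention clinics: "Training of providers on protocol and EHR changes as well as hypertension management will be done at intervention sites". Intervention description {11a} adds: "The training will be provided at the start of InterCARE and again annually". On blinding: "There was no blinding, as this is not feasible" (Who will be blinded {17a}).

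Individuals come after this. Eligibility criteria {10} admits people with a confirmed hypertension diagnosis or with a reading above threshold, and then says: "PLWH and HTN will be selected for enrolment using a purposive random sampling method by trained research assistants at each site". Implementation {16c} says: "Our research assistants will enroll participants who will then be exposed to the implementation strategies". Enrolment takes place mainly at HIV visits and, to raise numbers, also at laboratory and pharmacy visits (Recruitment {15}).

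In Statistical methods {20a}, the primary model has treatment as its only fixed effect, with clinic and pair as random effects. The adjusted model considers age, sex, education, income, waist-to-hip ratio or BMI, physical activity, smoking and alcohol.

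**The concern.** Randomising clinics balances clinics in expectation. It does not balance people who are chosen once the clinic's arm is known. Here three features coincide: the arm is known at site level, the sampling rule is unclear, and there are two entry routes with different starting points. Someone admitted on an elevated reading is above threshold at entry. Someone admitted on a recorded diagnosis may already be treated and controlled. If the mix of routes differs by arm, BP control can differ without any effect of the strategies.

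The term 'purposive random' does not settle how people were chosen: purposive sampling is by judgement and random sampling is not. Sequence generation {16a} considers only patients crossing between clinics, which is a different problem. At stake is the interpretation of the effectiveness co-primary outcome, above all if the observed difference is moderate.

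**Working it through.** **1. Order of events.** Clinic allocation, then activation as a labelled pair, then selection and enrolment by research assistants at the site. The article describes no participant list fixed before allocation, no arm-blind recruiter and no common random draw. Provider training stands among the launch steps, after the sentence on what happens before enrolment and ahead of the sentences on enrolling participants. It was probably done first, but the text does not time it explicitly.

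**2. What the analysis can absorb.** A shift in the same direction across pairs is indistinguishable from a treatment effect in a model with treatment fixed and clinic and pair random. Matching (Study setting {9}) is on staffing and patient numbers, with other clinic-level factors possible. Baseline BP, prior diagnosis and treatment at entry are not among the listed covariates.

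**3. The plan's own figures.** 14 × 333 = 4662, against 4652 stated. For power I used a matched-pair normal approximation with 7 − 2 = 5 effective pairs, m = 333 and ICC 0.055, so the design effect is 1 + 332 × 0.055 = 19.26.
- BP control, 19% v 64%: per-pair variance (0.1539 + 0.2304) × 19.26/333 = 0.0222; SE = √(0.0222/5) = 0.067; 0.45/0.067 ≈ 6.7; power above 99.9% (stated: above 99%).
- Prescribing, 57% v 80%: variance (0.2451 + 0.16) × 19.26/333 = 0.0234; SE 0.068; power 91.9% (stated: 93%).
- Minimum detectable difference for BP control: about 22 points (stated: 21).

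The plan's figures reproduce closely. Sample size is not at issue, because selection bias does not shrink with N.

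**4. Size of a possible bias (assumed inputs).** Bias = (difference between arms in the share entering on an elevated reading alone) × (difference in later control between the two routes). Neither factor is in the protocol. I assume 10 to 30 points for the first and 20 to 40 points for the second:
- 0.10 × 0.20 = 2 points
- 0.10 × 0.40 = 4 points
- 0.20 × 0.40 = 8 points
- 0.30 × 0.40 = 12 points

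The sign depends on which arm enrols more of which route, and on which route does better later.

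**5. Effect on the test when the strategies do nothing.** Inputs: 7 pairs; ICC 0.055; control-arm rate 19%; 333 × 0.9 × 0.9 = 269.7, taken as m = 269; equal clinics; the same bias in every pair. The design effect is 1 + 268 × 0.055 = 15.74. Per-pair variance = [0.1539 + p₁(1 − p₁)] × 15.74/269, where p₁ = 0.19 + bias. SE = √(variance/7). The rejection rate comes from the noncentral t with 6 df (two-sided critical value 2.447) and noncentrality bias/SE.

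| Bias favouring intervention | SE (points) | Noncentrality | Rejection rate |
|---|---|---|---|
| 0 | – | 0 | 5% |
| 2 points | 5.17 | 0.39 | 6.3% |
| 4 points | 5.26 | 0.76 | 9.9% |
| 8 points | 5.42 | 1.48 | 23.9% |
| 12 points | 5.54 | 2.16 | 44.4% |

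With m = 333 the rates are 6.3%, 10.0%, 24.1% and 44.8%. On the planned risk-ratio scale, 2 to 12 points on a 19% base gives a spurious ratio of 21/19 = 1.11 to 31/19 = 1.63. A bias of the same size in the other direction would make a true 21-point difference appear as 9 to 19 points.

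**The case against.** The strongest reply is that several links are inferred. The timing of training is not stated, and Implementation {16c} places exposure to the strategies after enrolment. The blinding section discusses providers, participants and analysts, and does not name recruiters. Research assistants enrol rather than the trained providers, both arms share the same numeric thresholds, and nothing says that EHR prompts feed the enrolment list. 'Purposive random' could mean a purposively defined pool sampled at random. The outcome is worded for people with diagnosed hypertension receiving medication, so some entrants on an elevated reading may not count until diagnosed; step 4 treats all of them as counted. Even 12 points is far below the targeted 45.

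Much of this stands, and it limits the claim. A reader might infer that recruiters demonstrably chose patients knowing the arm, that training certainly came first, or that the bias favours the intervention. The article supports none of these. Recruiters' knowledge of arm is a reasonable inference from working at activated, labelled, unblinded sites, but it is not stated. The direction can reverse, because elevated-reading entrants start uncontrolled.

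Two further replies do not remove the point. Reach includes the proportion of eligible people who enrol, but that does not describe who they are. Detail may be left to a SAP, but the article itself fixes the sampling wording and lists covariates that omit entry status.

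**Conclusion.** The point holds as a risk of recruitment bias that the stated analyses leave in the treatment estimate. It is not evidence that bias occurred. The protocol gives neither its direction nor its size. The 2 to 12 points, and the 6% to 44% false-positive risk when the bias favours the intervention, rest wholly on the assumed differences in step 4. The upper end needs both extremes, in the same direction in every pair. A result near 45 points could not be explained this way. A result near or below the stated 21-point detectable difference could be materially distorted, upwards or downwards. It should be addressed, with medium confidence.

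**What to change.** Recruitment is complete (Trial status), so the changes are to analysis and wording:

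1. Prespecify a supportive analysis of the BP-control co-primary outcome restricted to participants whose hypertension diagnosis was recorded before their clinic's launch date, where record dates allow.
2. Present the outcome by entry route: confirmed diagnosis, or elevated reading only.
3. Add baseline BP and treatment at entry to the adjusted model. BP, co-morbidities and medication are collected at baseline (Plans for assessment and collection of outcomes {18a}). The unadjusted primary model need not change.
4. Replace 'purposive random sampling' with the rule actually used, and state that enrolment followed allocation. Baseline BP, treatment and control by arm should accompany the result.

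The cost is a small amount of analysis and a few sentences, with no new participants. The restricted analysis is smaller and describes a narrower population. It depends on record quality, since clinics use both paper and electronic records and the article does not say that diagnosis dates are captured. It does not remove selection among people already diagnosed. If training did precede enrolment, baseline BP and treatment may already reflect it, so the adjusted result should be read as supportive.
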